#### Recruitment and consent procedures

Informed consent for Component 2 will be obtained prior to participation in Study 1. Once a participant has completed the baseline assessments of Component 1, the lead researcher ([name]) will contact participants who have consented to Component 2. All participants will be sent directions about setting up the space for the recording, which will be conducted either via videoconference call or as a self-recording by the participant. This method of remote data collection has been shown to be a feasible approach for caregivers (59).

#### Outcomes

##### Assessment of the parent-infant relationship

Videotaped parent-infant interaction will be rated for its global qualities using the *Manchester Assessment of Caregiver-Infant Interaction* (MACI-Infant) (60), a validated macroanalytic coding scheme. Coded videos of interaction are the “gold-standard” approach to assessing parent-infant relationship quality (61) and was included as a parent-infant attachment tool in a recent review of 25 measures by Shone et al. (62). MACI-Infant shows excellent stability over time, especially in maternal behaviours (60). The measure has been used in a range of populations including in mothers with mental health difficulties (63). MACI outcomes correlate with maternal and infant neural patterns (64–66), and empathy-specific mother-foetal attachment (67). MACI outcomes are also sensitive to change in interventions focused on enhancing the parent-infant relationship in other groups [e.g., (68)]. This assessment will allow us to examine whether the P-CFT group is associated with any enhancements in key parent-infant relational qualities. The MACI-Infant is suitable for infants aged 3 to 15 months old and consists of eight subscales, which are: 1) Caregiver sensitive responsiveness, 2) Caregiver non-directiveness, 3) Infant attentiveness to caregiver, 4) Infant positive affect, 5) Infant negative affect, 6) Infant liveliness, 7) Dyad mutuality, 8) Engagement intensity, and 9) Psychological stimulation. Each subscale is rated on a scale between 1 to 7. A score of 1 reflects a low frequency of a particular behaviour, and a score of 7 is indicative of a high frequency of a particular behaviour.

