#### Participant inclusion/exclusion criteria

Mothers and birthing parents are first referred to and assessed by the P-CMHT to determine their suitability for the service. If they meet the service criteria, they can be referred to the P-CFT group. Once enrolled to receive P-CFT and consent-to-contact is provided, the research team will assess a service user’s eligibility against the study criteria. To participate in the study, it is required that mothers^1^ are at least 18 years of age and have a baby that is less than two years old at the time of starting the P-CFT group OR they are currently pregnant and can complete the intervention prior to approximately 34 weeks gestation. Participants are excluded from the study if they are not receiving care from a P-CMHT, deemed unsuitable by the P-CMHT to receive a group intervention, assessed as acutely at risk of harm to their baby, experiencing acute psychotic symptoms, alcohol or substance misuse, active suicidality and/or lacking capacity to consent under the Mental Capacity Act 2005 (41).

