#### Participant inclusion/exclusion criteria

The inclusion and exclusion criteria applied to the overall study is largely consistent across Component 1 and Component 2. However, participants who are pregnant at baseline (Time 1) are excluded from Component 2, because a recording of the parent-infant dyad is required.

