#### Sample size consideration

Of the approximate 32 participants that completing the baseline assessment of Component 1, it is hoped that 50-75% of this sample will also consent to participate in Component 2. Therefore, Component 2 aims to recruit 16–22 parent-infant dyads, with ideally 5–8 participants collected from each research site.

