#### Procedure

Similarly to Component 1, the baseline recording for Component 2 will take place up to 4 weeks prior to the first treatment session (Time 1). Post-intervention (or Time 2) assessments will be undertaken after the intervention phase (which will be up to 4 weeks post-baseline assessments). Interactions will be recorded by either a remote call via secure videoconferencing [i.e., Microsoft Teams; (33)] or for participants to record the video using their own recording device. At the beginning of the call, the lead researcher ([name]) will guide the participant through the steps of the set-up. This set-up will involve setting up the computer/tablet/phone so that it is pointed to a corner of the room where the parent has brought some simple toys. The lead researcher will then record the interaction on the teleconferencing software and turn off their camera so that they are not visible to the participant for the duration of the play. For participants who self-record the interactions, participants will be asked to record only one six-minute interaction and send the lead researcher the video electronically.

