#### Coding and data analysis

By a trained researcher, the parent-infant interaction videos will be coded using the validated coding scheme, MACI-Infant. Researchers trained in the coding scheme ([name]) will complete coding, and a random selection of 50% of coded material will be double coded by a researcher to ensure reliability and accuracy. Researchers will be supervised by trained, research quality-compliant coders. Typically, each six-minute recording undergoes at least two reviews, with pauses to document the observation and initial ratings in conjunction with the manual. Subsequently, a final review of the interaction is conducted to establish the ratings. The parent-infant interaction ratings from pre- and post-intervention will be compared using an appropriate statistical test selected at the time of data analysis.

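### Component 2 admits any infant under two years, but its only rated interaction measure is stated to suit 3 to 15 months, so an unknown and possibly large share of dyads could be coded outside that range

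*Protocol article*

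**What the plan says.** All places are in the protocol article.

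- **Component 1, Participant inclusion/exclusion criteria.** A mother qualifies if she is pregnant (subject to a gestation limit) or if she is recorded to "have a baby that is less than two years old at the time of starting the P-CFT group". There is no lower age limit for the infant.
- **Component 2, Participant inclusion/exclusion criteria.** "The inclusion and exclusion criteria applied to the overall study is largely consistent across Component 1 and Component 2". One difference is then given: "participants who are pregnant at baseline (Time 1) are excluded from Component 2, because a recording of the parent-infant dyad is required".
- **Component 2, Assessment of the parent-infant relationship.** "The MACI-Infant is suitable for infants aged 3 to 15 months old and consists of eight subscales".
- **Component 2, Coding and data analysis.** "the parent-infant interaction videos will be coded using the validated coding scheme, MACI-Infant". No other scheme is named. Pre- and post-intervention ratings are to be compared.
- **Component 2, Sample size consideration.** Of about 32 Component 1 participants, "it is hoped that 50-75% of this sample will also consent to participate in Component 2", and so "Component 2 aims to recruit 16–22 parent-infant dyads, with ideally 5–8 participants collected from each research site".

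**The concern.** The eligibility text and the instrument's stated range do not match. The criteria admit 24 months of infant age, and the instrument is said to suit 12 of them. Infants under 3 months, and those older than 15 months, can be filmed and scored under the text as written.

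The comparison is pre versus post, so a dyad contributes a clean pair only if the infant is in range at both recordings. A dyad that starts in range and ages out mixes any change after the intervention with a change in how well the instrument fits. With about 16 to 22 dyads, a few such pairs can shift the result.

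The dyad target has a related problem. It is a percentage of all 32 participants, although pregnant participants cannot enter Component 2. The Discussion uses the Component 2 recruitment rate to indicate willingness to take part, and counting pregnant participants as non-takers would understate it.

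**Working it through.** **1. The plan's own target.**

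- 0.50 × 32 = 16, which matches the lower end.
- 0.75 × 32 = 24, against a stated 22; 22/32 = 68.75%.
- Per site: 3 × 5 = 15 and 3 × 8 = 24.

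The upper end is a small slip. Neither figure allows for pregnancy or infant age.

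**2. Interval between videos.** Inputs:

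- First video 0-4 weeks before session one (Component 2, Procedure).
- 8 to 12 sessions in consecutive weeks (Intervention and its delivery), so 7 to 11 weeks from first to last session.
- Second video 0-4 weeks after the intervention. This is the Component 1 window (Outcomes and assessments). The Component 2 Procedure section instead counts the 4 weeks from the baseline assessments, which cannot fit a course of 8 to 12 weekly sessions. The two sections need to be reconciled.

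Shortest gap: 0 + 7 + 0 = 7 weeks. Longest: 4 + 11 + 4 = 19 weeks. At 12/52.1775 months per week:

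- 7 weeks = 1.6 months
- 19 weeks = 4.4 months

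**3. First-video ages that keep both videos in range.** The lower limit is 3 months. The upper limit is 15 minus the gap:

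- 15 − 1.6 = 13.4 months (shortest gap)
- 15 − 4.4 = 10.6 months (longest gap)

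At the extreme, a child just under 24 months at group start could be 24 + (11 + 4) × 12/52.1775 = 27.4 months old at the second video.

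**4. Share of dyads in range at both videos.** The documents give no infant ages, so these distributions of age at group start are assumptions. With the shortest gap (first video at group start), the infant must be 3.0 to 13.4 months old at group start. With the longest gap (first video 4 weeks, or 0.92 months, earlier), the limits at group start are 3.92 and 11.55 months. For ages uniform over 0-24 months:

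- shortest gap: (13.39 − 3.00)/24 = 43%
- longest gap: (11.55 − 3.92)/24 = 32%

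The other rows follow in the same way.

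| Assumed age at group start | In range at both videos | Pairs of 16 | Pairs of 22 |
|---|---|---|---|
| Uniform 0-24 months | 32-43% | 5-7 | 7-10 |
| Uniform 0-18 months | 42-58% | 7-9 | 9-13 |
| Triangular 0-24, mode 6 | 53-68% | 9-11 | 12-15 |
| Uniform 0-12 months | 64-75% | 10-12 | 14-17 |
| Uniform 3-12 months | 85-100% | 14-16 | 19-22 |

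The loss therefore runs from none to about two thirds of pairs, depending on ages the documents do not report.

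**The case against.** Several objections have force.

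- **Extent.** A reader might infer that many videos will be out of range, or that fewer than 16 usable dyads will be found. The documents do not support either. The second inference needs a wide age spread such as uniform 0-24 months, where 32-43% of 32 is about 10-14. With ages uniform over 0-12 months, 64-75% of 32 is about 20-24 before pregnancy and consent.
- **Validity.** A reader might conclude that out-of-range ratings cannot be interpreted. The text says only that the instrument is suitable for 3 to 15 months. It does not say that ratings just outside are invalid.
- **Importance.** This is a single-group feasibility study, effects are an exploratory objective, and the numerical progression criterion concerns retention. No decision depends on change in MACI-Infant ratings.
- **Other outputs.** The Discussion also uses Component 2 to assess remote set-up, recording and willingness to take part. Infant age does not undermine these. Mothers of out-of-range infants are eligible as the text stands, so their answers do measure willingness; only pregnant participants clearly do not belong in the denominator.
- **Recoverability.** The baseline questionnaire already collects the age of the youngest child, so affected dyads can be identified at analysis.
- **Condensed article.** A fuller protocol might hold an age limit, and the Component 2 criteria are called only largely the same.

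The first five points limit size and severity, and they stand. The last is weak: the article does state Component 2 eligibility, with a named exception and a reason, and that exception is pregnancy alone. If an age limit exists elsewhere, this text misstates eligibility.

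**Conclusion.** The mismatch is real and nothing in the article resolves it: followed as written, the criteria allow dyads to be scored outside the age range the article gives for its only rated interaction measure, at one or both videos. The share is unknown and possibly large. The 32-43% and 85-100% figures are illustrations from assumed age distributions and a 7-19 week gap, not estimates for this sample. The 22-versus-24 slip is minor and does not bear on the age point. Severity is moderate: the pre-post MACI-Infant comparison is affected, while the remote-recording and willingness findings are not.

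**What to change.** 1. **Further recruitment.** Add to the Component 2 criteria that the infant is at least 3 months old at the first video and expected to be no older than 15 months at the second.
2. **Dyads already filmed.** Use the infant age already collected, with the recording dates, to base the main pre-post MACI-Infant comparison on pairs in range at both videos. Report the other pairs separately.
3. **Denominator.** Leave pregnant participants out of the denominator of the Component 2 recruitment rate. Once an age criterion applies, report uptake among age-eligible participants.
4. **Target.** Restate it: 50-75% of 32 is 16-24, before removing pregnant and out-of-range participants.
5. **Timing.** Reconcile the Component 2 post-intervention window with the Component 1 wording, since it determines how far infants age between videos.

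The cost is a minor amendment and a smaller Component 2 analysis sample, which should be stated. Recruitment began in November 2023, so the criterion cannot reach dyads already filmed; the analysis and denominator rules remain useful even after recruitment closes.

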#### Procedure

Similarly to Component 1, the baseline recording for Component 2 will take place up to 4 weeks prior to the first treatment session (Time 1). Post-intervention (or Time 2) assessments will be undertaken after the intervention phase (which will be up to 4 weeks post-baseline assessments). Interactions will be recorded by either a remote call via secure videoconferencing [i.e., Microsoft Teams; (33)] or for participants to record the video using their own recording device. At the beginning of the call, the lead researcher ([name]) will guide the participant through the steps of the set-up. This set-up will involve setting up the computer/tablet/phone so that it is pointed to a corner of the room where the parent has brought some simple toys. The lead researcher will then record the interaction on the teleconferencing software and turn off their camera so that they are not visible to the participant for the duration of the play. For participants who self-record the interactions, participants will be asked to record only one six-minute interaction and send the lead researcher the video electronically.

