**Methods:**

The multisite feasibility and acceptability study will adopt a single pre-post, quasi-experimental study design comprising three components using a sample of service users attending P-CFT groups. Component 1 is a feasibility study measuring maternal self-report questionnaire outcomes (e.g., self-compassion, postpartum bonding) at baseline, post-intervention and six-month follow-up, and recruitment and retention rates. Component 2 will evaluate mother-infant interactions through the coding of video observations from baseline to post-intervention. Component 3 will entail qualitative semi-structured interviews to explore the acceptability of the intervention. Data will be analysed using statistical methods of analysis for quantitative data (Component 1 and Component 2) and reflexive thematic analysis for qualitative data (Component 3).

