### Intervention and its delivery

The intervention is reported in line with the Template for Intervention Description and Replication (TIDieR) checklist (38), (see **Appendix A** in **Supplementary Materials** for further details). The group P-CFT intervention is based on Cree’s (11) adaptation of Gilbert’s (13, 14) CFT (see **Appendix B** for an overview of a P-CFT course). Whilst Cree’s (11) guidance is based on 12 sessions, the number of sessions can vary between services. In this study, the P-CFT intervention will range from eight to 12 sessions, which are to be delivered remotely via online video call platform Microsoft Teams (39) or in-person at a site of the perinatal CMHT. The two-hour sessions are offered once a week in consecutive weeks. There are two group facilitators in each group, and the number of participants can range from four to eight.

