#### Outcomes and assessments

For Component 1, participants will be asked to complete assessments at three time points. Baseline (or Time 1) assessments will be administered prior to the start of P-CFT (up to 4 weeks prior to the first treatment session). Post-intervention (or Time 2) assessments will be undertaken after the intervention phase (which will be up to 4 weeks post-intervention), with a final follow-up assessment at six months after baseline (referred to as Time 3).

Participants will be asked to complete a socio-demographic questionnaire which will provide information on the following: their NHS trust where they received P-CFT, current age, ethnicity, current relationship status, employment status, financial and socioeconomic situation, highest level of education, primary mental health diagnosis and whether or not they have received previous psychological treatment. The questionnaire will also collect data on age of youngest child and genders and ages of other children. At post-intervention, participants will be asked to provide the number of how many sessions of P-CFT they attended, as part of the online questionnaires.

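### The Component 2 window for the post-intervention video closes at 4 weeks after baseline, at least 3 weeks before any course can end

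*Protocol article*

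**What the plan says.** - **Component 2, Procedure.** The first video has a lead time: "the baseline recording for Component 2 will take place up to 4 weeks prior to the first treatment session (Time 1"). For the second, at Time 2: "assessments will be undertaken after the intervention phase (which will be up to 4 weeks post-baseline assessments").
- **Component 1, Outcomes and assessments.** The baseline lead is the same, "up to 4 weeks prior to the first treatment session". The Time 2 wording is nearly identical but has a different anchor: "assessments will be undertaken after the intervention phase (which will be up to 4 weeks post-intervention").
- **Intervention and its delivery.** On length, "the P-CFT intervention will range from eight to 12 sessions". On spacing, "The two-hour sessions are offered once a week in consecutive weeks".
- **Component 2, Design, and Table 1.** The Design section has the second recording made once the group has ended. Table 1 places the video in the Time 2 (post-intervention) column, which follows the intervention column.

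**The concern.** The Procedure sentence asks for a video that is both after treatment and within 4 weeks of baseline. No participant on a course of 8 or more weekly sessions can meet both conditions.

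What is at stake is the meaning of the Component 2 contrast. The Coding and data analysis section compares the MACI-Infant ratings before and after the intervention, and this is the study's only observed, rather than self-reported, measure of the parent-infant relationship. If someone scheduled the second video by the 4-week limit, it would come after about four sessions at most, or before the group had properly begun. The comparison would then not describe the completed course. Participants may record the video themselves and send it in, so the date on which it is requested decides what is measured.

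**Working it through.** This is calendar arithmetic in weeks, with baseline as week 0.

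**Inputs**
- Lead time L from baseline to first session: 0 to 4 (Component 2, Procedure; the same in Component 1).
- Number of weekly sessions k: 8 to 12 (Intervention and its delivery).
- Stated close of the Component 2 Time 2 window: 4 weeks after baseline.
- Component 1 Time 2 window: 0 to 4 weeks after the intervention.

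**Step 1: end of the course.** Counted to the date of the last session, the end is L + (k − 1). Counted as k full weeks, it is L + k.

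| Case | To last session | As full weeks |
|---|---|---|
| Earliest (L = 0, k = 8) | 0 + 7 = 7 | 0 + 8 = 8 |
| Latest (L = 4, k = 12) | 4 + 11 = 15 | 4 + 12 = 16 |

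Over both conventions, the course ends about 7 to 16 weeks after baseline.

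**Step 2: where the stated window closes relative to the course.** Time since the first session at closure is 4 − L, which runs from 4 − 0 = 4 weeks down to 4 − 4 = 0 weeks. At one extreme about four weekly sessions have been held; at the other the window closes at about the first session.

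**Step 3: gap between closure and the end of the course.** The gap is the end of the course minus 4. The smallest is 7 − 4 = 3 weeks and the largest is 16 − 4 = 12 weeks. No permitted combination of lead time and course length brings it to zero. Table 1 labels the intervention column as running to week 10 or 12; using 10 as the minimum only widens the smallest gap, to (0 + 9) − 4 = 5 weeks.

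**Step 4: the window with the Component 1 anchor.** The earliest second video is 7 + 0 = 7 weeks after baseline and the latest is 16 + 4 = 20 weeks. Every value in this range is after the course, which agrees with the Component 2 Design section and Table 1.

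**The case against.** The strongest reply is that the slip corrects itself. The same sentence says the video follows the intervention phase. The Design section, Table 1, the abstract and the analysis section all treat it as a post-intervention measure. The Procedure section introduces its timing as similar to Component 1, where the matching sentence counts from the end of the intervention. The component is optional and exploratory, within a feasibility study whose primary outcomes are recruitment, retention, attendance and questionnaire completion. Most of this stands: a one-word drafting error is the likeliest explanation, and a mistimed video would require someone to follow one parenthesis against everything around it. It does not remove the point, because the parenthesis is the only window stated for this video, and it is a wrong statement rather than detail left to a fuller document.

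The parenthesis might also be read as saying that the intervention phase begins within 4 weeks of baseline. The text does not say so. On that reading Component 2 would have no upper limit for its second video, and the sentence would still need correcting.

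A reader might go further and infer that the six-month follow-up is mislabelled too. The abstract lists assessments "at baseline, post-intervention and six-month follow-up, and recruitment and retention rates" without an anchor, and with six months taken as 26 weeks, Time 3 falls only 26 − 16 = 10 to 26 − 7 = 19 weeks after the course ends. The documents do not support calling this an error. Component 1 defines the visit openly, "with a final follow-up assessment at six months after baseline (referred to as Time 3"), the abstract merely condenses that, and nothing in the article claims durability six months after treatment. Anchoring follow-up to baseline is a legitimate choice, and how time since treatment enters the analysis is left open. The video is not collected at Time 3 in any case.

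**Conclusion.** The Component 2 Time 2 window is wrong as written. It closes 3 to 12 weeks before the course ends, and it contradicts the rest of its own sentence, the Component 2 Design section, Table 1 and the Component 1 window. This rests on sessions running weekly without gaps, as the article states; any missed week would only widen the gap. It holds whether the course is counted to the last session or in full weeks.

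The weight is that of a necessary but simple correction. A reader might infer that the pre-post video comparison is designed as a mid-treatment measure, or that videos have been taken too early. The article shows neither: its other statements consistently intend a measure after the group, and it reports no collection dates.

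**What to change.** In the Component 2 Procedure section, replace the post-baseline anchor in the Time 2 parenthesis with up to 4 weeks post-intervention, matching Component 1. The section then agrees with the Component 2 Design section and Table 1, and the MACI-Infant comparison refers to the completed course.

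The cost is one phrase, with no change to visits, sample or analysis. The Trial status section describes recruitment as ongoing until about March 2026, so on the article's own account the corrected wording can still guide collection. If any site instruction repeats the 4-week limit from baseline, it should be corrected at the same time.

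Optionally, the abstract could add that the six-month follow-up is counted from baseline. That is a courtesy to the reader, not a correction.
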